### Eligibility criteria

Patients with CP±L ages 24- to 32-months will be eligible if their parent consents to participate and will be available for the duration of the study. We will include participants who received palate surgery at least six months before enrollment, primarily speak English, Spanish, or both languages in the home, and have access to a smartphone or similar device (e.g., tablet) capable of recording and sharing video. Exclusions are diagnosed conditions that affect neurodevelopment (e.g., 22q11.2 deletion syndrome), profound sensory impairment (e.g., blindness, deafness), delivery < 32 weeks’ gestation, placement in foster care or state custody, or a diagnosis of autism spectrum disorder (ASD). Questions related to eligibility will be reviewed by one of the co-investigators (EG) and principal investigator (BC), and eligibility decisions will be documented to ensure consistency.

Staff from each site will complete an initial screening with parents to verify eligibility and obtain informed consent. Once parents consent to participate, baseline measures will be completed, including a demographic and clinical interview and parent-report measures (child expressive language, shared reading frequency). Parents will use their smartphones to record a video of themselves reading with their child and complete a speech task in which the child names a series of pictures. To ensure that families are able and willing to complete study procedures, we will only randomize participants if they complete at least one shared reading survey and upload at least one parent-child reading video at baseline. Parents will use a free app or online website to assess the need for broadband or cellular connectivity support to determine upload and download speeds. As needed, we will assist families with connectivity resources (e.g., a "hotspot") to ensure access to the intervention.

All participants will receive an end-of-study assessment. This will include any participants found to be ineligible after enrollment (e.g., those with new diagnoses) and participants who are not adherent to the intervention protocol or assessments.

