#### Clinician-administered measures

Clinician-administered measures will include the Expressive One-Word Picture Vocabulary Test—Fourth Edition (EOWPVT-4) and Receptive One-Word Picture Vocabulary Test—Fourth Edition (ROWPVT-4) for English-speaking families [24]. Both measures have large normative samples, including children as young as two years. For bilingual and Spanish-speaking children, the Spanish-bilingual editions will be used (EOWPVT-4:SBE and ROWPVT-4:SBE) [25, 26]. These measures were normed with a sample matched to the U.S. Latino/Hispanic population based on the 2010 U.S. Census. Bilingual participants are allowed to provide answers in English and Spanish. Correct responses in either language are credited for the total score, and the percentage of correct answers in each language is also calculated. The English and Spanish-Bilingual Editions of the EOWPVT-4 and ROWPVT-4 take about 20 minutes to administer. Reliability is excellent (i.e., internal consistency reliabilities > 0.94, test-retest reliabilities > 0.91), and both scales correlate with other language measures and differentiate children with and without language delays. Both measures have been used in several prior studies documenting the efficacy of DBS and similar interventions [13]. The choice of language for test administration will be based on parents’ reports of the child’s language exposure and production at home.

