### Sample size considerations and participant recruitment and retention

We determined the sample size (N = 320) based on the number of participants needed to ensure 80% power to test the hypothesis that children in the BOOST intervention group will have better receptive and expressive language skills than those in the SOC comparison group. Power analyses were based on two-sample unequal-variance t-tests, an alpha = 0.05/2 to adjust for multiple comparisons, and up to 20% attrition (i.e., final N~256). Under these assumptions, we will have 80% power to detect treatment group differences of >0.4 SD for our primary outcomes. Treatment effects this large have been observed in DBS studies with other non-cleft populations and are considered plausible and clinically meaningful [13].

Our assessment of longitudinal changes in child language during book-sharing interactions (Hypothesis 1b) will use a generalized estimating equations (GEE) approach to linear regression with robust standard error estimates. The outcome for these analyses will be observed child language, calculated as an average number of utterances, unique words used, and mean length of utterance. Analyses will test the effects of the intervention on children’s language during book-sharing interactions over the five observations. We will have > 80% power to detect changes with an effect size > 0.4 between any two time points and changes with effect sizes > 0.3 overall. Meta-analyses of similar interventions with non-cleft participants suggest that effect sizes this large or larger are observed and considered clinically meaningful. Similarly, we will have > 80% power to assess longitudinal changes in children’s language during book-sharing interactions, the quality and frequency of book-sharing interactions, and changes in parents’ book-sharing behaviors as a mediator of differences in children’s language outcomes.

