### Randomization

Half the participants will be randomly assigned to the BOOST Intervention Group (n = 160). The other half of the participants (n = 160) will be randomized to a SOC comparison group that receives the same children’s books, uploads shared reading videos, and responds to surveys but does not receive individualized BOOST intervention sessions. Randomization will be stratified by study site, families’ preferred language (English or Spanish), and Medicaid status. Randomization will be blocked in blocks of 4 to 6 participants to ensure reasonable balance in small strata.

A data manager will prepare randomization lists for all sites using REDCap under the direction of the study biostatistician. These lists will be concealed from all other study staff. Once a patient has been determined eligible for participation and randomization, the site coordinator will enter the participant into the study database and receive the treatment assignment via REDCap.

Staff completing outcomes assessments (e.g., observational coding of parent-child interactions, child language assessments) will be unaware of group assignments. Masking will not be feasible for some procedures that, by definition, reveal participants’ group assignment (e.g., observational measures of treatment fidelity). We will use restrictions on user privileges in REDCap to limit access to this information in project databases, and we will use password/code protections to restrict access to calendars, data archives used to store videos, and any other information that might reveal group randomization. Masked staff will not participate in meetings where group assignments may be revealed. If an assessor or observational coder becomes aware of a participant’s group assignment, we will identify another staff member to complete the assessment/coding.

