### Statistical methods

In analyses for our primary outcomes, we will use an intention-to-treat (ITT) approach to test the hypothesis that children in the BOOST group exhibit better language skills than children in the SCO comparison group. We will calculate 2-sample unequal-variance t-tests to estimate treatment versus control group differences in child language outcomes post-intervention. We will calculate standardized treatment effect sizes (ES) for all analyses to allow comparison across outcomes with different measurement scales. We will not adjust for covariates in the primary analyses. However, in sensitivity analyses, we will use bias-corrected ITT analyses to examine the robustness of treatment effects in the setting of non-adherence, missing data, or study attrition. To assess attrition bias, we will explore outcomes using Inverse Probability Weighting (IPW), with weights determined by the probability of having missing data or being lost to follow-up based on the RCT stratification variables and demographic and clinical data [39]. We will also conduct sensitivity analyses to examine the effects of variation in treatment fidelity using a weighting approach. Finally, we will examine the potential effects of children’s participation in other interventions in the community (e.g., speech and language therapy) using censored normal regression (CNR) [40].

Longitudinal analyses examining changes in child language during book-sharing and caregiver behaviors (i.e., quality and frequency of book-sharing) will use a GEE approach to linear regression with robust standard error estimates. This approach accounts for the correlation of observations over time and allows for the use of partial data on subjects who are lost to follow-up or non-compliant. Estimates will be adjusted for the RCT stratification variables, demographic confounds, and clinical characteristics (e.g., cleft type, age at cleft repair). Smoothing splines will be fit to examine changes in parents’ reading behaviors over time, including non-linear trends.

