### Limitations

Anticipated limitations and potential pitfalls for our study include limited generalizability to patients with clefts in conjunction with known genetic syndromes and other malformations. These groups are known to be at greater risk for poor neurodevelopmental outcomes, and we anticipated that their needs and response to intervention would likely differ. It is also possible that some patients will receive an exclusionary diagnosis (e.g., ASD) after study completion since these conditions may not be identified by 24- to 32-months. Developing similar interventions for children with syndromic conditions is a high priority. However, in this initial study, a more clinically homogeneous patient group was needed to establish intervention efficacy. Including English and Spanish-speaking participants complicates our outcomes assessment, given potential differences in language development for multi-lingual children. We have accounted for this by including language as a stratification variable in randomization, helping to ensure that the groups are balanced. The intensity of our intervention is another consideration, and we acknowledge that three 50-minute visits are modest. The results of meta-analyses have been somewhat contradictory on the minimum duration needed for similar interventions, with some indication that interventions of 90 minutes or greater produce significant treatment gains and others suggesting that longer duration is necessary for populations at significant risk for language delays [13, 14]. Ultimately, a lower-intensity intervention was needed to deliver the program at scale while minimizing participant burden and maximizing subsequent adaptation into standard cleft care. Finally, given the young age of our participants, there is a risk that our outcome measures will not be sensitive enough to detect treatment gains. Our multi-method assessment, including caregiver reports, clinician-administered measures, and observational measures of outcomes proximal to the intervention (e.g., changes in caregivers’ reading behaviors and changes in observed child language), is intended to address this concern.

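### The unadjusted primary t-test leaves out the stratification factors and the baseline vocabulary score: an avoidable loss of precision, not a bias

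*Protocol article*

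**What the plan says.** In the protocol article, Statistical methods fixes the primary test: "We will calculate 2-sample unequal-variance t-tests to estimate treatment versus control group differences in child language outcomes post-intervention". It then rules out adjustment: "We will not adjust for covariates in the primary analyses". No reason is given. The sensitivity analyses listed there deal with non-adherence, missing data, fidelity and community therapy. None is a treatment comparison adjusted for baseline score and strata. The same section does adjust the longitudinal GEE models for the stratification variables and uses those variables in the inverse probability weights.

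Under Randomization: "Randomization will be stratified by study site, families’ preferred language (English or Spanish), and Medicaid status", in blocks of 4 to 6. Under Eligibility criteria, after consent and before randomisation: "baseline measures will be completed, including a demographic and clinical interview and parent-report measures (child expressive language, shared reading frequency". Table 1 and Caregiver report measures identify the expressive language measure as the CDI-CAT, given at the first and final visits.

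The sample size section uses the same unadjusted test with "an alpha = 0.05/2 to adjust for multiple comparisons" and concludes that "we will have 80% power to detect treatment group differences of >0.4 SD for our primary outcomes", after 20% attrition from 320.

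On language, Clinician-administered measures says: "For bilingual and Spanish-speaking children, the Spanish-bilingual editions will be used (EOWPVT-4:SBE and ROWPVT-4:SBE". Limitations says of the mixed-language sample: "We have accounted for this by including language as a stratification variable in randomization, helping to ensure that the groups are balanced".

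**The concern.** Two kinds of information are available for the primary comparison and neither is used. They matter for different reasons.

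**The strata.** Stratified blocks hold the arms nearly equal on site, language and Medicaid status, so differences between strata contribute almost nothing to the true sampling variance of the arm difference. The t-test still counts those differences in its standard error. To the extent that the strata predict the outcome, the test is conservative and its interval too wide.

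**Baseline vocabulary.** Early expressive vocabulary is a natural predictor of language some months later. Without it the interval keeps its nominal coverage but is wider than it needs to be.

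At stake is the precision of the comparison that decides the trial. The detectable difference is close to the effect expected from the non-cleft literature (d about 0.4), and Limitations itself calls the intervention modest and warns that the measures may not be sensitive enough. Spare precision would be useful if the true effect is somewhat smaller.

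**Working it through.** **Inputs from the protocol article:** 320 randomised 1:1, 20% attrition, alpha 0.05/2 = 0.025, unequal-variance t-test, target 80% power at 0.4 SD. Strata: 3 sites × 2 languages × 2 Medicaid levels = 12 cells. **Assumptions:** a two-sided test (sidedness is not stated); the share of outcome variance explained by the strata, R²; and the correlation r between baseline CDI-CAT and the outcome. The article gives neither R² nor r, so ranges are shown.

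**1. The plan's own figure.** 320 × 0.8 = 256, or 128 per arm. Normal approximation: (2.2414 + 0.8416) × √(2/128) = 3.083 × 0.125 = 0.385 SD. Noncentral t gives 0.387 SD, which rounds to the stated 0.4. Power at exactly 0.40 SD is 82.7%. The number needed for 80% power at 0.40 SD is 2 × 3.083² / 0.4² = 118.8, so 119 per arm, 238 evaluable, and 238/0.8 = 298 randomised, below the planned 320. The stated figure holds.

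**2. Omitting the strata.** With near-perfect balance, the true variance of the difference is proportional to 1 − R², while the t-test estimates it as if proportional to 1. So true alpha = 2[1 − Φ(2.2414/√(1 − R²))], and the interval is too wide by a factor 1/√(1 − R²).

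| Assumed R² | True alpha (nominal 0.025) | Interval too wide by |
|---|---|---|
| 0.05 | 0.021 | 3% |
| 0.10 | 0.018 | 5% |
| 0.20 | 0.012 | 12% |

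A simulation with 12 strata, blocks of 4 or 6, 256 children and 4,000 runs per scenario agrees in direction and rough size. With no effect and strata shares of 0, 5, 10 and 20%, the t-test rejected in 2.9%, 2.2 to 2.5%, 1.6% and 1.4% of runs. A linear model with strata and baseline rejected in 2.3 to 2.7%. The Monte Carlo standard error near 0.025 is √(0.025 × 0.975/4000) = 0.0025, so the third decimal carries no weight. Both checks assume that the balance holds among the evaluable children. Attrition would loosen it, so the table is the upper end of the effect for each R².

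**3. Omitting baseline vocabulary.** Adjustment multiplies the residual SD by √(1 − r²), so the detectable difference is 0.387 × √(1 − r²). For r = 0.5 this is 0.387 × 0.866 = 0.335. Power is from the noncentral t at 128 per arm.

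| Assumed r | Interval width relative to unadjusted | Detectable difference, 80% power (SD) | Power at 0.40 SD | Power at 0.30 SD |
|---|---|---|---|---|
| 0 (unadjusted) | 1.00 | 0.387 | 82.7% | 55.8% |
| 0.3 | 0.95 | 0.369 | 86.4% | 60.3% |
| 0.4 | 0.92 | 0.355 | 89.1% | 64.2% |
| 0.5 | 0.87 | 0.335 | 92.4% | 69.7% |
| 0.6 | 0.80 | 0.310 | 95.9% | 77.1% |
| 0.7 | 0.71 | 0.277 | 98.7% | 86.5% |

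At r = 0.5 the adjusted analysis is worth 128/0.75 = 171 children per arm. The gains in steps 2 and 3 should not simply be added, because language and Medicaid status may themselves predict baseline vocabulary.

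**The case against.** The plan contains no error of validity. An unadjusted Welch test in a randomised trial is unbiased, does not inflate type I error, and is the test on which the trial was sized. This stands in full. A reader might infer that the trial is underpowered or its result biased; step 1 shows that the stated power is met, and nothing in the article points to bias. The 0.30 SD column concerns an effect that the primary test was not planned around.

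The size of the gain rests on assumed inputs. This also stands. A reader might infer that the delivered alpha is known to differ from 0.025. That holds only if the strata predict the outcome; with R² near zero the distortion disappears, and otherwise it is conservative.

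The CDI-CAT is an imperfect covariate. It is parent-reported and expressive only, whereas receptive language is also a primary outcome and Table 1 shows no baseline receptive measure. Its Spanish development sample ended at 30 months while entry runs to 32. It is planned for everyone but is not among the stated conditions for randomisation, so some scores may be missing. These points argue for the lower part of the r range, particularly for receptive language. They do not argue for omission.

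A reader might also infer that age must be in the model, or that pooling the English and Spanish-bilingual editions distorts the comparison. The article does not support either. The tests are normed, it does not say whether raw or standardised scores are analysed, and age-standardised scores would already remove most of the age effect. Preferred language is balanced by design, so pooling editions does not bias the arm comparison in expectation. Limitations claims balance, which stratification does provide; it makes no claim about the standard error.

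**Conclusion.** The point holds as an avoidable loss of precision of unknown size. The choice is stated outright in Statistical methods, so it is not a detail left to an unseen analysis plan. Under the assumptions shown (two-sided alpha 0.025, 128 evaluable per arm, strata R² of 5 to 20%, r of 0.3 to 0.7), the strata make the t-test mildly to moderately conservative, and baseline vocabulary could narrow the interval by 5 to 29%. Only the strata make the interval too wide in the strict sense of over-coverage. For baseline vocabulary the unadjusted interval is valid and simply less precise. Confidence is high that adjustment would help and low on how much, especially for receptive language. This is a free improvement and not a flaw that threatens the conclusions.

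**What to change.** For each primary outcome, prespecify a linear model of the end-of-study score on arm, baseline CDI-CAT score, site, preferred language and Medicaid status, with heteroscedasticity-robust standard errors. Handle a missing baseline score by simple imputation that does not use arm or outcome. Keep the Welch t-test as a sensitivity analysis.

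State whether raw or standardised scores are analysed. Add baseline age only if the scores are not age-standardised. Add test edition only if it is fixed from the baseline language report and the scores are not already on a common normed scale.

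Keep the sample size; the stated 80% power at 0.4 SD becomes a conservative floor. The cost is a short change to the protocol and analysis plan before outcome data are seen by arm. Enrolment is expected to run to about April 2028 and no interim outcome analyses are planned, so there is time. No new data are needed.

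### The longitudinal video analyses rely on unweighted GEE using partial data, so arm-differential loss tied to earlier language could bias Hypothesis 1b if the working correlation is independence

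*Protocol article*

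**What the plan says.** The protocol article, Statistical methods, says that the longitudinal analyses of child language during book-sharing and of caregiver behaviours "will use a GEE approach to linear regression with robust standard error estimates". It adds that the approach accounts for correlation over time and "allows for the use of partial data on subjects who are lost to follow-up or non-compliant". On covariates it says: "Estimates will be adjusted for the RCT stratification variables, demographic confounds, and clinical characteristics". It names no working correlation, weights or missing-data assumption for these models.

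The same section plans inverse probability weighting to assess attrition bias. That sentence stands in the paragraph on the primary outcomes, and the weights are to be "based on the RCT stratification variables and demographic and clinical data". Earlier observed language is not listed.

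The sample size section says Hypothesis 1b concerns "children’s language during book-sharing interactions over the five observations". It claims more than 80% power for effects above 0.4 between any two time points and for "changes with effect sizes > 0.3 overall".

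**The concern.** Unweighted GEE is in general consistent only if missingness is unrelated to observed outcomes, given the covariates in the model. Robust standard errors repair the variance, not a shifted mean. Here a family whose child says little on camera may stop uploading.

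The reasons for stopping may also differ by arm. In BOOST the interventionist reviews the videos between sessions, so uploading is part of treatment. In the comparison arm it is data collection only.

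If low-language children leave BOOST selectively, those who remain look better and the analysis can show a gain that is not there. If they leave the comparison arm selectively, a real gain is hidden. Hypothesis 1b and the quality of book-sharing are measured on these videos. Reading frequency uses the same model but comes from surveys, and no size was worked out for it.

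**Working it through.** **Inputs from the protocol article.** 160 children per arm; five videos; detectable effects of 0.4 (two time points) and 0.3 (overall); GEE covariates and weighting predictors as above. The Eligibility criteria section requires a baseline video before randomization, so only videos 2-5 can be missing.

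**Inputs assumed, because the article does not give them.** Within-child correlation ρ, the working correlation, video loss by arm, and how loss depends on language. The stated 20% attrition belongs to the primary-outcome power calculation and is borrowed here (128 per arm). The overall contrast is taken as the mean of videos 2-5 minus baseline.

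**1. The plan's power figures.** Outcome SD is 1, n = 128 per arm, two-sided 0.05.
- Two time points: SE = √[2 × 2(1−ρ)/n]. At ρ = 0.5, SE = √(2/128) = 0.125, 0.4/0.125 = 3.20, and power = Φ(3.20 − 1.96) = 89%. At ρ = 0.3 it is 77%.
- Overall: SE = √[2 × 1.25(1−ρ)/n]. At ρ = 0.5, SE = √(1.25/128) = 0.0988, 0.3/0.0988 = 3.04, and power = Φ(1.08) = 86%. At ρ = 0.3 it is 73%.

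The claim of more than 80% is plausible for ρ around 0.5-0.6, but cannot be confirmed without ρ.

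**2. How the bias arises.** With an independence working correlation and a separate mean for each arm and video, the fitted mean at video 5 is the mean of the children still contributing. If a proportion π is lost and those lost would have averaged δ SD below the arm mean, the remaining mean is too high by δπ/(1−π). Baseline is complete, so this passes straight into the change. With π = 0.20 and δ = 0.47, the shift is 0.47 × 0.20/0.80 = 0.12 SD. Equal shifts in the two arms cancel; opposite shifts add, 2 × 0.12 = 0.24 SD.

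**3. Simulation of the same mechanism.** 300,000 children per arm; monotone loss with log-odds linear in the previous video's language; true correlation exchangeable 0.4, exchangeable 0.6 or first-order autoregressive 0.8. Monte Carlo error is about 0.005 SD. Entries are absolute bias in SD across the three correlations.

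| Loss by video 5, and log-odds slope per SD | Independence: video 5 | Independence: overall | Exchangeable: video 5 |
|---|---|---|---|
| 20% in both arms, −1 in both | ≤0.004 | ≤0.004 | ≤0.003 |
| 10% v 30%, slope 0 in both | ≤0.005 | ≤0.003 | ≤0.004 |
| 20% in both, −0.5 in one arm only | 0.04-0.06 | 0.03-0.05 | ≤0.008 |
| 20% in both, −1 in one arm only | 0.08-0.12 | 0.05-0.08 | ≤0.017 |
| 10% v 30%, −1 in both | 0.08-0.12 | 0.05-0.08 | ≤0.016 |
| 10% v 30%, −1 in the 30% arm only | 0.12-0.18 | 0.08-0.12 | ≤0.020 |
| 20% in both, −1 v +1 (extreme) | 0.16-0.24 | 0.10-0.16 | ≤0.024 |

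So bias needs both dependence on language and a difference between arms in rate or mechanism. A working correlation matching the truth gave about 0-0.02 SD. A first-order autoregressive structure fitted to exchangeable data gave 0.01-0.08 SD (up to 0.12 in extreme cases).

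**4. The range carried forward.** With dependence in BOOST only, 20-30% loss in each arm and moderate correlation (exchangeable 0.5, autoregressive 0.6-0.7), independence GEE is biased by 0.04-0.15 SD at video 5, or 0.04/0.4 = 10% to 0.15/0.4 = 38% of that target. The overall contrast is biased by 0.03-0.10 SD, or 10% to 33% of 0.3. Extreme cases reach about 0.24 and 0.15 SD. Stronger correlation adds a little, as the table shows.

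**5. Consequence at the trial's size.** In 1,000 null trials per scenario with 160 per arm, independence GEE, slope −1 in BOOST only and 20-30% loss, the false-positive rate was 9-18% against a nominal 5%. A baseline covariate explaining an assumed 20% of language variance cut the bias to 0.04-0.08 SD and the false-positive rate to 6-10%.

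**The case against.** The strongest reply is that the plan has not said anything false. It says GEE can use partial data, which it can. A reader might infer that the plan credits GEE with removing dropout bias; the text does not say so.

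A reader might also infer that GEE is invalid whenever loss depends on earlier language. That is too absolute. For a continuous outcome with correct means and a nearly correct working correlation, GEE behaves almost like a likelihood analysis and the bias almost disappears. The sizeable figures need an independence structure, which the article does not name and a statistical analysis plan may rule out.

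The loss patterns are assumed too, and opposite dependence in the two arms is an extreme case. The baseline-video requirement and the $40 payment per video should limit loss. The article lists child language during book-sharing under intermediate and exploratory outcomes; the primary outcomes use t-tests.

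All of this stands and keeps the point small. It does not remove it. The article's one stated provision for missing videos is the use of partial data. The planned weighting is placed with the primary outcomes, and even if extended to the videos, its listed predictors would not fully correct loss driven by earlier language. The GEE covariates are of the same kind. Hypothesis 1b is also a numbered hypothesis with its own power claim.

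**Conclusion.** The point holds in a limited, conditional form. Nothing stated in the article protects the video analyses if loss depends on earlier language differently by arm. Under an independence working correlation that could move the arm difference in change to video 5 by roughly 0.04-0.15 SD, and the overall contrast by about 0.03-0.10 SD, with extremes near 0.24 and 0.15 SD. Every size rests on assumed loss, dependence and correlation. The documents do not support the stronger conclusion that the Hypothesis 1b estimate will be biased: with the same rate and mechanism of loss in both arms, or a well-chosen working correlation, bias is close to zero. This is a minor improvement to a non-primary analysis.

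**What to change.** State the missing-data assumption for the longitudinal models and adopt one of two routes.

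- Fit a likelihood-based mixed model with the same arm-by-time means and an unstructured covariance, as the main analysis or as a stated check on the GEE. With five videos the covariance has 5 × 6/2 = 15 parameters, which 320 children can support.
- Or keep GEE with an independence working correlation and weight by arm-specific inverse probabilities of still contributing videos, with earlier video language among the predictors.

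Both brought bias to about zero in the check when the covariance or weight model was correct. Do not combine observation-level weights with an exchangeable or unstructured working correlation: weights with an exchangeable structure gave bias of about 0.02-0.10 SD in the opposite direction.

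The cost is wording and code. The predictor is already collected, since every randomized child has a baseline video. The mixed model relies on its covariance model, and the weights add some variability. Neither route covers loss that depends on language not observed.
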